**Appendix 6**

### Jasikan IPTc delivery system study

### Adverse event reporting form

Community ………………….

Child’s First Name………………………… Last name……………………..

Child’s ID Number: |___|___|___|___|___|

Mother’s First name……………………………Last name…..……………….

**Notified adverse events** [Y] [N]

If yes,

| Adverse event | Date onset | Time onset | End date | End time | Severity |
| --- | --- | --- | --- | --- | --- |
| General bodily weakness |  |  |  |  |  |
| drowsiness |  |  |  |  |  |
| Difficulty in breathing |  |  |  |  |  |
| Vomiting |  |  |  |  |  |
| Cannot sleep |  |  |  |  |  |
| Cannot eat |  |  |  |  |  |
| Other |  |  |  |  |  |
| Other |  |  |  |  |  |
| Other |  |  |  |  |  |

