**7.2 Screening for eligibility**

Children whose parents or guardians wanted their wards to participate will be assessed by the research team for eligibility for enrolment into the study: Children with the following conditions will be excluded from the study: (1) severe malnutrition; (2) chronic diarrhoea; (3) history of convulsions; (4) prostration, extreme weakness (inability to stand or sit); (5) history of hypersensitivity to AQ or SP. The study staff will examine the children for these criteria at the time of pre intervention cross sectional survey and refer children having any of these conditions to the PI for the final decision.

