**7.7 Cross-sectional surveys**

Two cross-sectional surveys will be undertaken in May and November 2006. The first survey will be the pre-intervention survey which will provide baseline information about the study children and the second one will be a post- intervention survey. In both surveys, information to be collected will include the background information about the child and mother/guardian, history of allergy to any of the study drugs, bednet ownership and use, measurement of temperature and anthropometric indices. This will also involve collection of finger prick blood samples for determination of asexual and sexual parasitaemia.

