**7.11 Assessment of adverse Events**

***Eliciting and documenting adverse experiences***

All adverse events or reactions, which occur during the trial, will be documented. The nature of each experience, date and time (where appropriate) of onset, duration, severity and relationship to treatment will be established whenever possible.

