**Mother/Guardian’s**

First Name………………………………Last Name…………………………………..

Age (in yrs [ ] Occupation…………………..

House No………Landmark………………………………………………………………

|  | **Inclusion criteria** | **Yes** | **No** |
| --- | --- | --- | --- |
| 1 | Age between 3 to 59 months |  |  |
| 2 | Resident in the community for at least the next six months |  |  |
| 3 | Has parent or guardian given consent |  |  |
| 4 | Child unable to take or retain medication |  |  |
| 5 | Existence of respiratory distress |  |  |
| 6 | Existence of serious or chronic illness |  |  |
|  | **Exclusion criteria** |  |  |
| 1 | History of drug allergy |  |  |
|  | **Measurement** | **Record measurement** | |
| 1 | Temperature |  |  |

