| 14. Diarrhoea …………………………………………….. | | | yes | 1 |  | no | 2 | |  | | dk | 8 |  |
| 14a. If has diarrhoea, what is the type of stool | | Watery | **1** |  | Bloody | | **2** | |  | Other | | **3** |  |
|  | | | | | | | | | | | | | |
| 15.Vomiting …………………………………………. | | | yes | 1 |  | no | 2 | |  | | dk | 8 |  |
| 16. Fits during this illness ………………………… | | | yes | 1 |  | no | 2 | |  | | dk | 8 |  |
| 16a. If the child has fits, number of fits in 24 hours ……………………………… | | | | | | | | | | |  |  |  |
| 17. Itching/ scratching (pruritus)…………………… | | | yes | 1 |  | no | 2 | |  | | dk | 8 |  |
| 18. Did the child receive any of the following drugs before coming to the clinic for the present illness? | | | | | | | | | | | | | |
| A. SP (fansider) | | | yes | 1 |  | no | 2 | |  | | dk | 8 |  |
| B. Other antimalarials (specify) ______________________ | | | yes | 1 |  | no | 2 | |  | | dk | 8 |  |
| C. Antibiotics …………………………………………………… | | | yes | 1 |  | no | 2 | |  | | dk | 8 |  |
| D. Vitamins/iron …………………………………………….. | | | yes | 1 |  | no | 2 | |  | | dk | 8 |  |
| E. others (specify) ___________________________ | | | yes | 1 |  | no | 2 | |  | | dk | 8 |  |
|  | | | | | | | | | | | |  |  |
| **19. If the child had received any drug, from where?** | A. Home | | yes | 1 |  | no | 2 | |  | | dk | 8 |  |
|  | B. Shop | | yes | 1 |  | no | 2 | |  | | dk | 8 |  |
|  | C. Clinic/hosp | | yes | 1 |  | no | 2 | |  | | dk | 8 |  |
| (If others, specify) ______________________________ | D. Others | | yes | 1 |  | no | 2 | |  | | dk | 8 |  |

Please look for the following signs

| 20. Weight (kg) ………………………………………………………………….. | | | | | | | | | | | | | | | | | | | |  | |  | | · |  | Kg |
| --- | --- | --- | --- | --- | --- | --- | --- | --- | --- | --- | --- | --- | --- | --- | --- | --- | --- | --- | --- | --- | --- | --- | --- | --- | --- | --- |
|  | | | | | | | | | | | | | | | | | | | | | | | | | | |
| 21. Axillary Temp. (ºC) ………………………………………………………… | | | | | | | | | | | | | | | | | | | |  | |  | | · |  | ˚C |
|  | | | | | | | | | | | | | | | | | | | | | | | | | | |
| 22. Pale conjunctiva……. …………………………………….. | | | | | | | | | | | yes | | | | 1 | |  | | no | 2 | |  | | ns | 8 |  |
|  | | | | | | | | | | | | | | | | | | | | | | | | | | |
| 23. Jaundice ………………..………………………………….. | | | | | | | | | | | yes | | | | 1 | |  | | no | | 2 | |  | ns | 8 |  |
|  | | | | | | | | | | | | | | | | | | | | | | | | | | |

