| 24. Mouth sores (stomatitis)………….………………………… | | | | | | | | | | | yes | | | | 1 | |  | | no | | 2 | |  | ns | 8 |  |
|  | | | | | | | | | | | | | | | | | | | | | | | | | | |
| 25. Pale palms………………………….………………………. | | | | | | | | | | | yes | | | | 1 | |  | | no | | 2 | |  | ns | 8 |  |
|  | | | | | | | | | | | | | | | | | | | | | | | | | | |
| 26. Skin rash (specify) _____________________________ | | | | | | | | | | | yes | | | | 1 | |  | | no | | 2 | |  | ns | 8 |  |
|  | | | | | | | | | | | | | | | | | | | | | | | | | | |
| 27. Nasal flaring ……………………………………..……….. | | | | | | | | | | | yes | | | | 1 | |  | | no | | 2 | |  | ns | 8 |  |
|  | | | | | | | | | | | | | | | | | | | | | | | | | | |
| 28.Chest indrawing ……………………………………………. | | | | | | | | | | | yes | | | | 1 | |  | | no | | 2 | |  | ns | 8 |  |
|  | | | | | | | | | | | | | | | | | | | | | | | | | | |
| 29. Respiratory rate per minute ………………………………………………………… | | | | | | | | | | | | | | | | | | | | | | |  |  |  |  |
|  | | | | | | | | | | | | | | | | | | | | | | | | | | |
| 30 Mucous membrane …………………………………… | | | | | | | | | | dry | | | | **1** | |  | | Normal | | | **2** | |  | ns | **8** |  |
|  | | | | | | | | | | | | | | | | | | | | | | | | | | |
| **31 Skin turgor ……………………………………………** | | | | | | | | | | reduced | | | | **1** | |  | | normal | | | **2** | |  | ns | **8** |  |
|  | | | | | | | | | | | | | | | | | | | | | | | | | | |
| 32. Oedema ……………………………………………......... | | | | | | | | | | | yes | | | | 1 | |  | | no | | 2 | |  | ns | 8 |  |
|  | | | | | | | | | | | | | | | | | | | | | | | | | | |
| 33. Pus in ear ………………………………………………… | | | | | | | | | | | yes | | | | 1 | |  | | no | | 2 | |  | ns | 8 |  |
|  | | | | | | | | | | | | | | | | | | | | | | | | | | |
| 34. Neck stiffness …………………………………………… | | | | | | | | | | | yes | | | | 1 | |  | | no | | 2 | |  | ns | 8 |  |
|  | | | | | | | | | | | | | | | | | | | | | | | | | | |
| 35. Level of consciousness …………………… | | | | | | | | | Normal | | **1** | |  | | Abnormal | | | | | | **2** |  | | ns | **8** |  |
|  | | | | | | | | | | | | | | | | | | | | | | | | | | |
| 36 Fontenella | | **n**ormal | **1** |  | sunken | **2** |  | bulging | | **3** |  | ns | | | **8** | |  | | not applicable | | | | | | **9** |  |
|  | | | | | | | | | | | | | | | | | | | | | | | | |  | |
|  | Take blood samples for examining malaria parasites and HB | | | | | | | | | | | | | | | | | | | | | | | | |  |
|  | | | | | | | | | | | | | | | | | | | | | | | | | | |

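### The adverse event form prompts for no skin, mouth or liver sign, so such reactions after AQ+SP could be recorded incompletely and unevenly between arms

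*Protocol*

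**What the plan says.** Section 7.11 sets a broad rule: "All adverse events or reactions, which occur during the trial, will be documented". It asks for onset, duration, severity and relation to treatment where these can be established. It also ties the reporting of serious events to those arising within 24 hours of a dose.

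The dedicated form is Appendix 6. It names six symptoms: "General bodily weakness", drowsiness, "Difficulty in breathing", vomiting, sleeplessness and not eating. Three rows marked only as other follow. Each row has space for onset, end and severity. Under section 7.6, village coordinators are trained to fill in the form, and health centre distributors receive the same training.

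Allergy to the drugs appears in three other places:
- The eligibility section (7.2) lists "history of hypersensitivity to AQ or SP" among five exclusions.
- The screening form (Appendix 2) has a single item under its exclusion heading, "History of drug allergy".
- Both cross-sectional surveys (7.7) collect "history of allergy to any of the study drugs".

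The outpatient form (Appendix 7) has fixed rows for "17. Itching/ scratching (pruritus" and "26. Skin rash (specify", and for jaundice (item 23) and mouth sores (item 24). The inpatient form (Appendix 8) repeats all four.

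**The concern.** The study team thought these four signs worth a tick-box on its clinic forms but gave them none on the one form devoted to adverse events. A form with a printed list tends to return what is on the list. Anything else depends on the person filling it in recognising the sign as an event and writing it down.

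That person differs by arm: a village volunteer in the community arm, a member of health staff in the facility arm. If one group writes in unprompted signs more readily than the other, the recorded frequency of skin reactions could differ between arms because of the recorder. A low overall count could likewise reflect the form. What is at stake is the safety record that the DSMB reviews.

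**Working it through.** No figure in the protocol bears on this and no formula applies. The check is a comparison of forms and of the routes by which a reaction could reach the record.

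**Items on the forms**

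| Sign | Appendix 6 | Appendix 7 | Appendix 8 |
| --- | --- | --- | --- |
| Itching | no row | item 17 | item 17 |
| Jaundice | no row | item 23 | item 23 |
| Mouth sores | no row | item 24 | item 24 |
| Skin rash | no row | item 26 | item 26 |

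Appendix 6 therefore has six named prompts, three open rows, and none of the four signs. The inpatient form also asks about an enlarged liver. Of the six prompts, "Difficulty in breathing" could be part of an allergic reaction. The other five are non-specific.

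**Routes other than Appendix 6**

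1. *Clinic forms.* These prompt for all four signs, but only in children brought to a surveillance facility or admitted.
2. *Home visits (7.8, Appendix 9).* Field workers go out four days after the first dose and ask about side effects, but only of a random selection of mothers. Appendix 9 has three blank event rows and no named symptom, and its lead question concerns events during drug administration.
3. *November survey (7.7).* All recruited children are included (7.4), and study-drug allergy is asked about directly. Section 7.7 lists this as one history item and specifies neither sign nor date. It comes five to six months after the first course, which the protocol places in June in 7.8 and 7.10 and in May in 7.1.

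For a child who is not brought to a facility and whose mother is not selected for a visit, what remains is an unprompted entry on Appendix 6 and the November question.

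**Timing.** Appendix 6 has onset date and time but no date or number of the preceding course. The dates of the four courses are on the child's identification card (Appendix 3), so timing an entry against the 24-hour window in 7.11 needs a second record.

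**Scale of exposure.** Section 7.5 expects about 960 children. With four courses each, that is at most 960 × 4 = 3,840 courses. This is the number of occasions on which a reaction could arise. It is not an estimate of how many would be missed.

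**The case against.** The strongest reply is that nothing here contradicts the protocol. The rule in 7.11 covers every event, Appendix 6 opens with an unrestricted yes/no question and has three free rows, and distributors are trained to use it. Rash or itching is unprompted, not excluded. Which symptoms to print is a matter of form design. That stands, and it limits the point to a weakness in a form that the protocol itself fixes.

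Further, the home visits, the survey question and the advice to parents in 7.9 to bring a child with any sign of illness to a health centre all add capture. This also stands, but only in part: each route either reaches some of the children or asks once, late and without detail.

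Dose dates, admissions and deaths are recorded elsewhere (Appendix 3, section 7.9, Appendix 8), so their absence from Appendix 6 does not mean that they are lost. Linking and tabulating these records may properly be left to a statistical analysis plan. That part of the objection is accepted. A course date on the form is a convenience for timing and does not repair a missing record.

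Two stronger readings are tempting. A reader might infer that reactions *would* be under-reported, or try to attach a percentage. The documents give no reaction rate, no attendance rate and no rate of unprompted entries, so neither is supported. A reader might also infer that these four signs are the reactions most specific to AQ+SP. The protocol does not say so: on the clinic forms they sit in a general illness checklist beside runny nose and pus in the ear. It does not call hypersensitivity the main drug risk either. That is an inference from its exclusion criteria.

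**Conclusion.** The point holds as a form-design weakness that should be put right. Itching, rash, mouth sores and jaundice after a course can reach Appendix 6 only unprompted. In children not seen at a facility, they could be under-recorded and recorded unevenly between arms. The other routes offset this in part, and its size cannot be estimated from the documents.

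The conclusion rests on two assumptions: that prompting affects what is recorded and does so differently for volunteers and health staff, and that Appendix 5, which is not in the text available, does not already supply these prompts. Adverse events are not among the listed endpoints. The primary coverage endpoint and the sample size are unaffected.

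**What to change.** In Appendix 6, add pre-printed rows for itching, skin rash, mouth sores and jaundice, worded as in Appendix 7 items 17, 26, 24 and 23, and keep the open rows. Add the date and number of the last IPTc course, so that an entry can be timed against the 24-hour reporting window in 7.11 without a second document. A date alone places the event to the nearest day.

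The cost is reprinting one form before distributors are trained on it. The downside is small: prompted rows will also collect some rashes unrelated to the drugs, and the course date helps in judging those. The change affects data capture only and leaves dosing and clinical management as they are.

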**Appendix 7**

# JASIKAN IPTc DELIVERY SYSTEM STUDY Out Patient Surveillance Form (OPS FORM)

|  | 1. ID NUMBER | | | |  | |  |  | |  |  |  | | | | | | | | | | | | | | | | | | | | | | | | |
| --- | --- | --- | --- | --- | --- | --- | --- | --- | --- | --- | --- | --- | --- | --- | --- | --- | --- | --- | --- | --- | --- | --- | --- | --- | --- | --- | --- | --- | --- | --- | --- | --- | --- | --- | --- | --- |
|  | | | | | | | | | | | |  | | | |  | | |  | | |  | | |  |  |  |  |  |  |  |  |  |  |  |  |
| 2. Name of Health facility __________________ | 3A. CLINIC CODE | | | | | | |  | |  |  |  | | |  |  |  |  |  |  |  |  | | | | | | | | | | | | | | |
|  | 3b. DELIVERY SYSTEM | | | | | | |  | |  |  |  | | |  |  |  |  |  |  |  |  | | | | | | | | | | | | | | |
| 4 .Name of child ___________________________________ | | | | | | | | | | | |  | | |  |  |  |  |  |  |  |  |  |  |  | | | | | | | | | | | |
|  | | | | | | | | | | | |  | | | | | | | | | | | | | | | | | | | | | | | | |
| 5. Date of birth (date/month/year) ………………………………………… | | | |  | |  |  |  | |  |  |  |  | | | | | | | | | | | | | | | | | | | | | | | |
|  | | | | | | | | | | | |  | | | | | | | | | | | | | | | | | | | | | | | | |
| 6. Sex of child …………………………………………….. | | **m**ale | | | **1** | |  | | **f**emale | | **2** |  | |  | | | | | | | | | | | | | | | | | | | | | | |
|  | | | | | | | | | | | |  | | | | | | | | | | | | | | | | | | | | | | | | |
| 7. Date of exam. (date/month/year) ………………………………………….. | | |  | |  | |  |  | |  |  |  |  | | | | | | | | | | | | | | | | | | | | | | | |

| Ask whether the child has any of the following symptoms | | | | | | | | | | | | | |
| --- | --- | --- | --- | --- | --- | --- | --- | --- | --- | --- | --- | --- | --- |
| 8. Can the child suckle/drink?................................................... | | | yes | **1** |  | no | | **2** |  | | dk | **8** |  |
|  | | | | | | | | | | | | | |
| 9. Fever within the past 2 days…………………………….. | | | yes | **1** |  | no | | **2** |  | | dk | **8** |  |
| 10. If the child has fever, how many days? ……………………………………………………. | | | | | | | | | | |  |  |  |
| 11. Runny nose ……………………………………………. | | | yes | 1 |  | no | 2 | |  | | dk | 8 |  |
|  | | | | | | | | | | | | | |
| 12. Cough …………………………………………………. | | | yes | 1 |  | no | 2 | |  | | dk | 8 |  |
|  | | | | | | | | | | | | | |
| 13. Difficulty in breathing ……………………………….. | | | yes | 1 |  | no | 2 | |  | | dk | 8 |  |
|  | | | | | | | | | | | | | |
| 14. Diarrhoea …………………………………………….. | | | yes | 1 |  | no | 2 | |  | | dk | 8 |  |
| 14a. If has diarrhoea, what is the type of stool | | Watery | **1** |  | Bloody | | **2** | |  | Other | | **3** |  |
|  | | | | | | | | | | | | | |
| 15.Vomiting …………………………………………. | | | yes | 1 |  | no | 2 | |  | | dk | 8 |  |
| 16. Fits during this illness ………………………… | | | yes | 1 |  | no | 2 | |  | | dk | 8 |  |
| 16a. If the child has fits, number of fits in 24 hours ……………………………… | | | | | | | | | | |  |  |  |
| 17. Itching/ scratching (pruritus)…………………… | | | yes | 1 |  | no | 2 | |  | | dk | 8 |  |
| 18. Did the child receive any of the following drugs before coming to the clinic for the present illness? | | | | | | | | | | | | | |
| A. SP (fansider) | | | yes | 1 |  | no | 2 | |  | | dk | 8 |  |
| B. Other antimalarials (specify) ______________________ | | | yes | 1 |  | no | 2 | |  | | dk | 8 |  |
| C. Antibiotics …………………………………………………… | | | yes | 1 |  | no | 2 | |  | | dk | 8 |  |
| D. Vitamins/iron …………………………………………….. | | | yes | 1 |  | no | 2 | |  | | dk | 8 |  |
| E. others (specify) ___________________________ | | | yes | 1 |  | no | 2 | |  | | dk | 8 |  |
|  | | | | | | | | | | | |  |  |
| **19. If the child had received any drug, from where?** | A. Home | | yes | 1 |  | no | 2 | |  | | dk | 8 |  |
|  | B. Shop | | yes | 1 |  | no | 2 | |  | | dk | 8 |  |
|  | C. Clinic/hosp | | yes | 1 |  | no | 2 | |  | | dk | 8 |  |
| (If others, specify) ______________________________ | D. Others | | yes | 1 |  | no | 2 | |  | | dk | 8 |  |

Please look for the following signs

| 20. Weight (kg) ………………………………………………………………….. | | | | | | | | | | | | | | | | | | | |  | |  | | · |  | Kg |
| --- | --- | --- | --- | --- | --- | --- | --- | --- | --- | --- | --- | --- | --- | --- | --- | --- | --- | --- | --- | --- | --- | --- | --- | --- | --- | --- |
|  | | | | | | | | | | | | | | | | | | | | | | | | | | |
| 21. Axillary Temp. (ºC) ………………………………………………………… | | | | | | | | | | | | | | | | | | | |  | |  | | · |  | ˚C |
|  | | | | | | | | | | | | | | | | | | | | | | | | | | |
| 22. Pale conjunctiva……. …………………………………….. | | | | | | | | | | | yes | | | | 1 | |  | | no | 2 | |  | | ns | 8 |  |
|  | | | | | | | | | | | | | | | | | | | | | | | | | | |
| 23. Jaundice ………………..………………………………….. | | | | | | | | | | | yes | | | | 1 | |  | | no | | 2 | |  | ns | 8 |  |
|  | | | | | | | | | | | | | | | | | | | | | | | | | | |
| 24. Mouth sores (stomatitis)………….………………………… | | | | | | | | | | | yes | | | | 1 | |  | | no | | 2 | |  | ns | 8 |  |
|  | | | | | | | | | | | | | | | | | | | | | | | | | | |
| 25. Pale palms………………………….………………………. | | | | | | | | | | | yes | | | | 1 | |  | | no | | 2 | |  | ns | 8 |  |
|  | | | | | | | | | | | | | | | | | | | | | | | | | | |
| 26. Skin rash (specify) _____________________________ | | | | | | | | | | | yes | | | | 1 | |  | | no | | 2 | |  | ns | 8 |  |
|  | | | | | | | | | | | | | | | | | | | | | | | | | | |
| 27. Nasal flaring ……………………………………..……….. | | | | | | | | | | | yes | | | | 1 | |  | | no | | 2 | |  | ns | 8 |  |
|  | | | | | | | | | | | | | | | | | | | | | | | | | | |
| 28.Chest indrawing ……………………………………………. | | | | | | | | | | | yes | | | | 1 | |  | | no | | 2 | |  | ns | 8 |  |
|  | | | | | | | | | | | | | | | | | | | | | | | | | | |
| 29. Respiratory rate per minute ………………………………………………………… | | | | | | | | | | | | | | | | | | | | | | |  |  |  |  |
|  | | | | | | | | | | | | | | | | | | | | | | | | | | |
| 30 Mucous membrane …………………………………… | | | | | | | | | | dry | | | | **1** | |  | | Normal | | | **2** | |  | ns | **8** |  |
|  | | | | | | | | | | | | | | | | | | | | | | | | | | |
| **31 Skin turgor ……………………………………………** | | | | | | | | | | reduced | | | | **1** | |  | | normal | | | **2** | |  | ns | **8** |  |
|  | | | | | | | | | | | | | | | | | | | | | | | | | | |
| 32. Oedema ……………………………………………......... | | | | | | | | | | | yes | | | | 1 | |  | | no | | 2 | |  | ns | 8 |  |
|  | | | | | | | | | | | | | | | | | | | | | | | | | | |
| 33. Pus in ear ………………………………………………… | | | | | | | | | | | yes | | | | 1 | |  | | no | | 2 | |  | ns | 8 |  |
|  | | | | | | | | | | | | | | | | | | | | | | | | | | |
| 34. Neck stiffness …………………………………………… | | | | | | | | | | | yes | | | | 1 | |  | | no | | 2 | |  | ns | 8 |  |
|  | | | | | | | | | | | | | | | | | | | | | | | | | | |
| 35. Level of consciousness …………………… | | | | | | | | | Normal | | **1** | |  | | Abnormal | | | | | | **2** |  | | ns | **8** |  |
|  | | | | | | | | | | | | | | | | | | | | | | | | | | |
| 36 Fontenella | | **n**ormal | **1** |  | sunken | **2** |  | bulging | | **3** |  | ns | | | **8** | |  | | not applicable | | | | | | **9** |  |
|  | | | | | | | | | | | | | | | | | | | | | | | | |  | |
|  | Take blood samples for examining malaria parasites and HB | | | | | | | | | | | | | | | | | | | | | | | | |  |
|  | | | | | | | | | | | | | | | | | | | | | | | | | | |
| 37. Blood slide taken ……………………………………….. | | | | | | | | | | | yes | | | | 1 | |  | | no | 2 | | |  | ns | 8 |  |
| **37a. If blood slide was not taken specify the reason(s) __________________________________** | | | | | | | | | | | | | | | | | | | | | | | | | | |
|  | | | | | | | | | | | | | | | | | | | | | | | | | | |
| 38. Haemoglobin checked | | | | | | | | | | | yes | | | | 1 | |  | | no | 2 | | |  | ns | 8 |  |
|  | | | | | | | | | | | | | | | | | | | | | | | | | | |
| **38a. If HB was not checked specify the reason(s) __________________________________** | | | | | | | | | | | | | | | | | | | | | | | | | | |

| 39. Blood slide result | positive | 1 |  | Negative | 2 |  | nS | 8 |  | not applicable | | | | 9 |  |
| --- | --- | --- | --- | --- | --- | --- | --- | --- | --- | --- | --- | --- | --- | --- | --- |
|  | | | | | | | | | | | | | | | |
| 40. Hb (G/DL) ………………………………………………………… | | | | | | | | | | |  |  |  |  |  |

Record your Diagnosis and the Treatment given to the child

| 41. Diagnosis _____________________________________________ | | | | | | | | | | | | | | | | |  |  |  |
| --- | --- | --- | --- | --- | --- | --- | --- | --- | --- | --- | --- | --- | --- | --- | --- | --- | --- | --- | --- |
|  | | | | | | | | | | | | | | | | | | | |
| 42. Antimalarial (specify) ____________________________ | | | | | yes | | | 1 |  | no | 2 | | |  | | | ns | 8 |  |
|  | | | | | | | | | | | | | | | | | | | |
| 43. Antibiotics (specify) ___________________________ | | | | | yes | | | 1 |  | no | | 2 | | |  | | ns | 8 |  |
|  | | | | | | | | | | | | | | | | | | | |
| 44. Antihistamine (specify)__________________________ | | | | | yes | | | 1 |  | no | | 2 | | |  | | ns | 8 |  |
|  | | | | | | | | | | | | | | | | | | | |
| 44. Other drugs (Speccify) ____________________________ | | | | | yes | | | 1 |  | no | | 2 | | |  | | ns | 8 |  |
|  | | | | | | | | | | | | | | | | | | | |
| 45. Management plan | Home care | 1 |  | admitted | | 2 |  | referred | | | | | 8 |  | | ns | | 8 |  |
|  | | | | | | | | | | | | | | | | | | | |
| 46. Outpatient surveillance form completed by………………………………………………….. | | | | | | | | | | | | | | | | |  |  |  |

**DK** = Do not know; **NS** = Not sure

